##### IBD and RA cohorts

For RA patients, the biologics registry will be screened, and eligible participants directed towards the research team. For IBD patients, potential participants will be identified from the nurse-led biologic clinic attended by those commencing a new biologic. A selection of patients may be identified by the IBD multidisciplinary meetings during discussions of standards of care.

Invitations to participate in the study will occur via face to face interaction during clinic and patient information sheets (PIS) distribution through post or email to eligible patients by the clinical research teams. We will then contact the patient up to 4 weeks after they have received the PIS to discuss their potential participation. The patient will be free to refuse to take part or withdraw from the study at any time and this decision will not affect their care.

##### Control cohort

Poster advertising recruitment will be disseminated across the University of Birmingham, targeting staff and students. All participants who volunteer will then be screened for eligibility.

#### Study schedule and method

This study entails four visits spanning a 24-week period. Figure 1 provides an overview of the duration and assessment carried out for each visit. Some of the visits may occur outside of the selected time frames for each visit, for example, to accommodate LT, unexpected illness or events that can occur during their participation. If patients have been admitted during the timing of a visit, we will seek permission from the team overseeing their care and the patient, for participation if clinically safe and feasible to do so.

**Fig. 1 Fig1:**
[figure not shown]
Flow chart to summarise each visit and time point of the study and the assessments performed

#### Experimental variables

The primary experimental variables for this study are:To identify the best non-invasive assessment parameters to evaluate sarcopenia in CLD, IBD and RA and acquire data for the degree of sarcopenia in each disease cohort (muscle area, strength, functional state and activity indices).To identify any longitudinal change in measures as determined by change in muscle mass, strength and function over a 6-month period, in concordance with their clinical status and treatment.

The disease-specific secondary experimental variables related to mechanisms potentially driving sarcopenia are highlighted in Table 2.

**Table 2 Tab2:** Secondary outcome measures

CLD	IBD	RA
• Change in model for end-stage liver disease (MELD) scores over the 24-week period. • Complications of CLD (frequency of ascitic paracentesis, number of hospital admissions, the incidence of serious infections such a spontaneous bacterial peritonitis). • For those who undergo LT, post-operative complications, e.g. length of admission. • Transplant free survival time. • Quality of life measures. • Physical activity indices.	• Change in clinical status. • Change in mucosal healing, as defined by Travis et al, [45], symptoms scoring including Harvey Bradshaw Index scoring and severity staging including Mayo scoring. • Complications of IBD (number of hospital admissions, number of acute flares). • Quality of Life measures. • Physical activity indices.	• Change in disease activity (ACR response criteria, DAS28 response, achievement of ACR/EULAR remission criteria). • Complications of RA (number of hospital admissions, number of acute flares) • Quality of life measures. • Physical activity indices.

#### Assessment modalities

We will carry out the following assessments as described below.*Full clinical history and examination*: including a full set of routine observations.*Assessment of blood samples*: C reactive protein, ESR, baseline renal function, liver function, full blood count, clotting function, vitamin D, ferritin, folate, vitamin B12, thyroid function, lipids, and trace elements (zinc, selenium and vitamin A) [46]; cytokine and adipokine panel (interleukin (IL)IL1β, IL4, IL6, IL8, IL10, IL12, IL13, IL16, IL17, IL23, IL33, ILIRA, tumour necrosis factor alpha (TNFα), leptin, ghrelin, adiponectin) will be measured by Luminex [47]; serum cortisol, cortisone, dehydroepiandrosterone (DHEA), dehydroepiandrosterone sulphate (DHEA-S) and 3-methyl histidine (assessing skeletal muscle catabolism) by mass spectrometry [48, 49]; peripheral blood mononuclear cells (PBMCs) will be collected and stored at – 80 °C for future analysis of the degree of immune ageing.*Urine and stool sampling*: A 30-ml urine and 30-g stool sample from the preceding 36 h will be collected and stored for metabolomic, inflammatory and microbiome analysis (dependent on further funding).*Anthropometric assessment*: Age, weight, height, waist and hip circumference, and body mass index will be measured. Bioelectrical impedance analysis will be performed to estimate percentage body fat and fat-free mass [1]. Hand grip strength (HGS), mid-arm muscle circumference (MAMC) and triceps skinfold thickness (TSF) will be determined.*Functional assessment*: This will include accelerometry, Short Physical Performance Battery (SPPB) testing and isokinetic dynamometry.Accelerometry: Physical activity, sedentary time and sleep duration and quality will be evaluated using a GeneActiv accelerometer wristwatch, worn for 14 days prior to visits 2,3, and 4.SPPB: This measure is validated to predict mortality through the assessment of gait speed (time to walk 4 metres), standing balance and repeated chair stands (sit to stand test). This is scored out of a maximum of 12 points, with a maximum of 4 in each domain [50, 51].Isokinetic dynamometry: This measures strength and power via knee extension. Maximal muscle strength will be measured as the peak torque [52].*Muscle imaging*: Ultrasonographic (US) imaging of the quadriceps will measure muscle size, architecture and quality. Magnetic resonance imaging (MRI) will be used to assess muscle size (cross-sectional area, (ACSA), muscle volume of quadriceps and muscle quality (through intramuscular fat measures, myosteatosis and echogenicity of the muscle). All image results will undergo a review by Consultant Musculoskeletal Radiologist.*Muscle tissue evaluation*: A biopsy of the vastus lateralis will be performed from the dominant leg at visits 2 and 4 to evaluate muscle fibre structure and fibre phenotyping via immunohistochemistry. Biomolecular analysis of key anabolic and catabolic pathways, including genomic, epigenomic and transcriptomic analysis will be performed to give further understanding of the processes driving sarcopenia.An urgent blood test will be performed on the day of biopsy, to check clotting and platelet function are within criteria, if one has not already been performed within the preceding two weeks.*Quality of Life (QoL) assessment*: This will be measured using two validated questionnaires. All participants will be asked to complete the Short Form-36 (SF-36) health-related QoL questionnaire (Quality Metric Health Outcomes Solutions, Lincoln, USA) [53]. It is a practical, reliable, and validated measure of physical and mental health.

Each cohort will be asked to complete a disease-specific validated tool:CLD cohort - Chronic Liver Disease Questionnaire (CLDQ): A 29-item tool that evaluates the following domains: fatigue, activity, emotional function, abdominal symptoms, systemic symptoms, and worry [54].RA cohort - Functional Assessment of Chronic Illness Therapy – Fatigue (FACIT-F) Questionnaire: A 13-item tool that evaluates the following domains: physical, social, emotional and functional wellbeing to measure an individual’s level of fatigue during their usual daily activities over the past week [55].IBD cohort - Inflammatory Bowel Disease – Disability Index (IBD -DI): A 28-item tool that evaluates activity and participation, body structures and environmental factors [21].

*Nutritional evaluation* will be carried out for the two weeks preceding each interval review, via a 14-day food diary [8]. Diet Plan 7 (Forestfield Software Limited) will be used to calculate the macro and micronutrient intake accordingly.

Table 3 highlights the methods for performing some of the assessments in detail.

**Table 3 Tab3:** Methodology for measurements

Measurement	Method
Hang grip strength	Three trials with a rest of 30 s between the tests will be performed for each hand, with a handheld Takei digital dynamometer and patients will be encouraged to exert their maximal grip strength [1, 56]. An average value will be calculated.
MAMC	This is the midpoint between the lateral edge of the acromion and olecranon process of the radius, on the mid line of the posterior surface of the dominant arm; it is measured with the arm in a supine position, flexed at the elbow with the forearm rotated against the body at 90 degrees, and the hand resting against the torso. Once the midpoint is marked, the arm returns to a supine position with the hand against the thigh. The MAMC is measured around the midpoint mark ensuring the measuring tape is even against the skin (without being taut). This will be repeated twice, and the mean result calculated.
TSF	From the midpoint calculated above, a vertical pinch with a Harpenden calliper, parallel to the long axis of the arm, is made at the landmark in a perpendicular direction. Measurement in millimetres will be taken; it will be repeated twice, and a mean is calculated [57–59].
Isokinetic dynamometry	This measures strength and power via knee extension. Maximal muscle strength will be measured as the peak torque [52]. Patients will be seated in an adjustable, straight-backed chair with their hips and their knees flexed at 90°; their pelvis and the thighs will be secured by a broad strap with their arms crossed in front of their chest. After the instruction and 2-3 practical trials, the patient will be asked to extend, then flex the leg with maximal effort, for 5 repetitions. Both legs will be tested, unless contraindicated by pain or other symptoms. Unilateral limb tests will be performed on the non-biopsied leg, following a muscle biopsy [60, 61].
US scan	Patients will lie in a semi-supine position with legs resting flat on a bed. All images will be taken at 50 % of femur length (measured from the greater trochanter to the lateral knee joint space). The maximal anatomical ACSA of human quadriceps is shown to be at ~50% of the femur length [62]. Two-dimensional B-mode ultrasonography Esoate MyLab Alpha point of care ultrasound, 4.6 cm probe (SL1543, 13-4Mhz scanning frequency)) will be performed. Three longitudinal scans will be taken at 50% femur length of the vastus lateralis muscle with the probe aligned to the fascicles; allowing for quantification of fascicle length and pennation angle. Vastus lateralis muscle thickness (defined as the perpendicular distance between the superficial and deeper aponeurosis) will be obtained. All variables will be obtained offline via image J imaging software and will be presented as a mean. For assessment of all quadricep muscles, two extended field of view ultrasound images will be taken at 50% femur length; this will allow for the quantification of quadriceps ACSA. Echogenicity can be determined using a computer-assisted grey-scale analysis offered by ImageJ [63, 64].
MRI femur	Axial and sagittal plane scans of each thigh will be obtained using an MR 3T scanner for higher quality, efficient imaging capture and 3D reconstruction. A T1 weighted Spin Echo protocol will be used (repetition time 600ms, echo time 15.2 ms, Field of view 512 × 512 mm, slice thickness 10mm, no gap between slices). Patients will lie supine on a preparation bed for up to 20 min to allow fluid shift stabilisation. A series of axial plane scans along the entire length of the quadriceps muscle group and sections at the L3 lumbar spine (L3 lumbar spine to quadriceps insertion on the tibia) will be collected. The contours of the quadriceps will be digitalised offline using the Osirix DICOM image analysis software (Pixmeo, Geneva, Switzerland) and the quadriceps muscle volume will be calculated [65]. 3-dimensional acquisition of both thighs and a Dixon sequence will be performed for fat analysis. Quadriceps muscle ACSA will be measured as described in the above. This midpoint of each femur length and the midpoint of VL (which is where ultrasound CSA measurements are taken from) will be marked with an external marker to ensure this is identified on MR images for analysis purposes and comparisons with ultrasound measurements. All image results will undergo a review by Consultant Musculoskeletal Radiologist.
Muscle biopsy	The patient will be fasted for ~6 h prior to the procedure. The ultrasound performed will identify the correct position to ensuring the sample is taken from the muscle belly. The non-dominant limb will be used if the dominant limb is not feasible. A small area of skin overlying the outer thigh will be cleaned with iodine solution. 5–10ml of 1% lignocaine is infiltrated into the subcutaneous adipose tissue and down to the muscle. After adequate anaesthetic, a small incision is made in the skin (approximately 5–7mm in length). A needle is inserted into the muscle and a small amount of muscle is taken using a well-described technique with a Bergstrom needle. A few passes may be performed. The incision will be closed using ‘steri-strips’ and a single suture, if required. A small dressing will then be placed over the biopsy site. Pressure and an ice compress will be applied to the area for 10 min by hand. A pressure bandage which will stay on for 8 h to decrease the risk of bruise formation. Patients will be asked to keep this area dry for at 3–5 days. All patients will receive after care advice and contact if any problems do arise.

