### Chronic liver disease

A significant proportion of patients with CLD have a degree of malnutrition and this is closely associated with sarcopenia [8, 9]. Muscle wasting within CLD can be due to several factors including altered metabolism and inactivity. Protein-energy malnutrition is very common in patients with liver cirrhosis (estimated at 65–90%) [10]. Mechanisms reducing protein synthesis and enhancing degradation such as accelerated starvation where glycogen depletion occurs, insulin resistance and hyperammonaemia predominate in CLD [10, 11]. It is becoming increasingly clear that the degree of sarcopenia is directly related to outcomes in patients with liver disease. In a recent study of 130 patients with cirrhosis, survival at 5 years was 50% in those with sarcopenia at baseline, compared to 80% without sarcopenia at baseline [12]. In a study of 669 cirrhotic patients assessed for transplantation in Canada and the USA, sarcopenia was present in 45% of the patients and they had a median survival of 20 months compared to 95 months for those without sarcopenia [13].

In liver disease, sarcopenia may be hidden by either oedema masking muscle loss, or obesity [14, 15]. Current prognostic indicators such as the Royal Free Hospital Global Assessment (RFH GA) tool, or scoring systems such as Child-Pugh score and Model for End Stage Liver Disease (MELD) [16] score based on anthropometry/nutritional assessment of patients, may thus have reduced sensitivity in the presence of these relatively common confounders. This can underestimate the risk for those with sarcopenia and reduce the validity of assessing and prioritising patients for liver transplant surgery. In addition, since muscle mass is a static reflection of the health of the musculoskeletal system, it is also important to assess dynamic aspects such as strength, power and fatigability.

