### Statistical analysis plan

All quantitative data will be entered into a purpose-designed database and exported for statistical analysis in relevant statistical software. Members of the research team, including a statistician, will conduct the analysis. The analyses that will be performed will include:The extent of sarcopenia in the three target chronic inflammatory diseases using several methods to assess muscle mass, function and strength and compare these data with the EWGSOP criteria.Identification of potential mechanisms of sarcopenia that occur in CLD, IBD and RA achieved through a multi-modal assessment process.Assessment of any longitudinal changes in each cohort over a 6-month period following their standard of care.Assessment of the best non-invasive assessment parameters for evaluation of sarcopenia will be made via analysis of the results of anthropometric, functional, and imaging data, using non-parametric analysis via Spearman correlation. Specifically, we will carry out the following:Baseline descriptions of clinical parameters and sarcopenia with proportions demonstrated and median and mean formulated.Correlation analysis of measures of sarcopenia and how they relate to disease severity, QoL, etc., will be performed by qualitative measures.Comparisons between disease types will be made using non-paired, non-parametric testing.Dynamic changes over 6-months (pre and post 6-months of standard of care treatment) will be assessed using paired, parametric and non-parametric testing.

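### Table 3 labels a whole-arm tape reading as mid-arm muscle circumference, so one of the study's muscle-mass measures includes subcutaneous fat

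*Protocol article*

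**What the plan says.** Under Assessment modalities, the anthropometric paragraph lists the two arm measures as separate variables: "Hand grip strength (HGS), mid-arm muscle circumference (MAMC) and triceps skinfold thickness (TSF) will be determined".

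Table 3 then gives the method. After the midpoint of the upper arm has been marked, the MAMC row says: "The MAMC is measured around the midpoint mark ensuring the measuring tape is even against the skin (without being taut"). It ends: "This will be repeated twice, and the mean result calculated". The row therefore runs from landmark to final value, and the final value is an average of tape readings.

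The next row takes the skinfold at the same place: "From the midpoint calculated above, a vertical pinch with a Harpenden calliper, parallel to the long axis of the arm". It is recorded in millimetres and averaged on its own. Nowhere does the article combine the skinfold with the circumference, and it names no separate mid-arm circumference.

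The Statistical analysis plan section says that the best non-invasive parameters will be assessed "via analysis of the results of anthropometric, functional, and imaging data, using non-parametric analysis via Spearman correlation". Under Experimental variables, the choice of those parameters is a primary variable, and so is change in muscle mass, strength and function over 6 months.

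**The concern.** A tape laid on the skin encloses skin, subcutaneous fat, muscle and bone. It gives the circumference of the arm. To call that reading the muscle circumference attaches the name of one quantity to the method for another.

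A constant error would matter little, because it would leave ranks and changes intact. This error varies with each patient's fat layer. Two things are then at stake:

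- **Ranks.** Spearman correlation uses ranks. If fat shifts them, MAMC may look like a better or worse marker of muscle than it is.
- **Change.** In any 6-month comparison of MAMC, gain or loss of subcutaneous fat would be read as gain or loss of muscle.

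The Background section on chronic liver disease raises the same hazard: "In liver disease, sarcopenia may be hidden by either oedema masking muscle loss, or obesity". The study also recruits a NAFLD subset for comparison.

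**Working it through.** The article states no figure for this measure, so there is nothing to reproduce. The check is geometric, followed by a range of assumptions.

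**Inputs**
- From Table 3: the tape reading C is taken over the skin at the midpoint; TSF is taken at the same midpoint, in mm.
- Assumed, because the article gives no values: arm circumference, TSF, and their spread.

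**Formula.** A skinfold is a double layer, so the fat rim is TSF/2 thick. For a circular arm with an even rim,

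muscle circumference = C - 2 x pi x (TSF/2) = C - pi x TSF (same units).

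Recording C as MAMC therefore overstates it by pi x TSF, whatever the size of the arm.

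**Size in one patient (assumed 30 cm arm)**

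| TSF | Overstatement | Derived MAMC | Excess over derived value |
|---|---|---|---|
| 5 mm | pi x 0.5 = 1.6 cm | 28.4 cm | 5.5% |
| 15 mm | pi x 1.5 = 4.7 cm | 25.3 cm | 18.6% |
| 30 mm | pi x 3.0 = 9.4 cm | 20.6 cm | 45.8% |

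**Ranks can reverse.** A constructed pair shows this:
- Arm 34 cm, TSF 30 mm: 34 - 9.4 = 24.6 cm.
- Arm 28 cm, TSF 8 mm: 28 - 2.5 = 25.5 cm.

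The tape puts the first patient 6 cm ahead; the derived value puts that patient 0.9 cm behind.

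**Change over time.** Change in C = change in MAMC + pi x change in TSF. An assumed 5 mm rise in TSF with no change in muscle moves the tape reading by 1.6 cm.

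**Effect on correlations.** Let M be the true MAMC with assumed SD 2.5 cm, let F = pi x TSF, and let M and F be uncorrelated. Then

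corr(C, M) = SD(M) / sqrt(SD(M)^2 + SD(F)^2) and corr(C, TSF) = SD(F) / sqrt(SD(M)^2 + SD(F)^2).

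| Assumed TSF SD | SD(F) | Pearson with muscle | Pearson with TSF |
|---|---|---|---|
| 4 mm | 1.26 cm | 0.89 | 0.45 |
| 6 mm | 1.88 cm | 0.80 | 0.60 |
| 8 mm | 2.51 cm | 0.71 | 0.71 |
| 10 mm | 3.14 cm | 0.62 | 0.78 |

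With an assumed muscle-fat correlation of 0.3, the figures over the same range are 0.92 down to 0.75 with muscle and 0.64 up to 0.85 with TSF.

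**The case against.** **The article is condensed.** Table 3 describes only some assessments, its rows tell an operator how to take a reading, and a derivation formula could sit in the full protocol, the CRF or the analysis plan. The article also uses its verbs loosely: body mass index is said to be measured although it is computed. The two inputs for a derived MAMC are taken at one landmark, which may mean that the subtraction is intended. This stands as a reason to allow that the database may already be right. It does not clear the text, because the MAMC row does not stop at a raw reading: it says that the MAMC is what the tape measures and carries it through to a mean.

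**MAMC is a minor measure.** This largely stands. It enters the analysis only under the general term for anthropometric data. The section on challenges in study design does not name it among its examples of validated and newer measures. MRI, ultrasound and bioimpedance also cover muscle quantity.

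**Stronger readings that the document does not support.**
- A reader might infer that the error would hide sarcopenia in NAFLD or other obese patients. The article gives no MAMC cut-off and no MAMC-based classification; extent is compared with the EWGSOP criteria, and other measures can supply muscle quantity.
- A reader might infer that the recorded value tracks fat as strongly as muscle. That is so at a TSF SD of 8 mm; at 4 mm the reading still tracks mainly muscle.
- A reader might infer that the subtraction also solves the oedema problem. It removes the fold thickness only, does not cleanly remove oedema, and leaves bone in.

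**Conclusion.** The fault is real but limited. As written, Table 3 yields whole-arm circumference under the name of muscle circumference, too large by pi x TSF. The direction of the error and its growth with fat do not depend on any assumed value; the formula rests on a circular arm and an even fat rim. The centimetre figures follow from the chosen TSF values, and the percentages also from the assumed 30 cm arm. The loss of correlation with muscle rests on assumed SDs and could be slight (0.89) or substantial (0.62).

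The consequence is that one of several muscle-mass measures could be misranked in the Spearman analysis and misread in any 6-month comparison that uses it. The article does not show that any patient would be misclassified for sarcopenia, or that a primary conclusion rests on MAMC alone. No data are lost, because both inputs are already planned at the same site.

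**What to change.** 1. In Table 3 and the CRF, name the tape reading mid-arm circumference (MAC).
2. Define MAMC (cm) = mean MAC (cm) - pi x mean TSF (cm), with TSF converted from mm and both means from the same visit.
3. Derive MAMC this way for all visits, including those already recorded, and use the derived value as the muscle measure in the correlation and change analyses.
4. State the limits beside the definition: bone remains included and oedema is not cleanly removed.
5. If the database already applies the subtraction, correct Table 3 to say so.

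The cost is one derived variable and a wording change; no new measurement is needed.
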